**Exclusion criteria**
- Life expectancy lower than 3 months (as assessed by the treating physician)
- Living in residential or institutional care prior to the cardiac arrest

The sample size calculation (two groups and one-sided testing) results from research on traumatic brain injured patients with regard to their participation in society assessed using the Community Integration Questionnaire (CIQ, described in more detail later). The mean (sd) total score on the CIQ was 16.09 (sd = 4.20) [28]. An assumed clinical relevant difference between groups of at least 10%, an alpha of 0.05 and a power (1-β) of 0.8 would necessitate 84 patients in each group. With an estimated loss to follow-up of 15%, based on earlier research in cardiac arrest survivors, 200 participants are thought to be necessary for the clinical trial [19,21,29]. This should be achievable within three years, as the area served by the participating hospitals covers approximately 1,000,000 inhabitants.

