### Recruitment and randomisation

Between three and ten days after the cardiac arrest the patient and caregiver will be approached to participate in the study by their treating physician. Standard procedures concerning informed consent will be used. Both patients and caregivers sign an informed consent form if they decide to participate in the study. In case the patient is still unconscious or incapacitated at the moment that informed consent is needed, the caregiver will be asked to give provisional informed consent. When the patient regains consciousness, definitive informed consent will be sought.

Participants will be randomly allocated to either the intervention group or the control group. The randomisation will take place after the baseline measurements (2 weeks after the cardiac arrest) and will be performed centrally by the project leader using a computerised block randomisation. The randomisation scheme includes prestratification on two variables, namely hospital site and location of the cardiac arrest (in-hospital versus out-of hospital). Two series of opaque numbered envelopes will be prepared for each hospital site (one for in-hospital and one for out-of-hospital cardiac arrests), filled with a card indicating the allocated group. After registration, the envelope will be opened and the specialised nurse will be informed about the patients that are allocated to the intervention group.

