### Statistical analysis

#### Effect evaluation

Descriptive techniques will be used to present data concerning the participants, number of dropouts, losses-to-follow up and the scores on the outcome measures.

To determine whether the patients participating in this trial are representative for the population of cardiac arrest survivors, the baseline characteristics between compliant and non-compliant participants, as well as dropouts and losses-to-follow up will be compared.

Before examining the effectiveness of the intervention, the comparability of the two groups will be checked. Baseline characteristics will be compared using independent sample T-test (normal distribution) or Mann Whitney U-test (non-normal distribution), in case of a continuous variable. In case of a dichotomous variable a chi-square test will be used.

The data from the evaluation study will be analysed according to the intention-to-treatment principle. If either T1 or T2 data are missing the 'last-observation-carried-forward' principle will be used.

Multiple regression analysis, adjusted for possible differences in baseline characteristics or baseline scores, will be applied to examine differences between the intervention and the control group on the primary outcome measures at T3 (one year after the cardiac arrest). If there is a difference between the groups, the effect size will be calculated. Subgroup analysis will be performed for potential effect modifiers.

To assess whether protocol deviations or care provided outside the intervention have caused biases, the results of the intention-to-treatment analysis will be compared to the on-treatment analysis.

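### Adjustment in the primary regression is tied to observed baseline differences, which makes the model data-dependent and tends to leave out the baseline score and the randomisation strata

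*Protocol article*

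**What the plan says.** Under Statistical analysis, Effect evaluation, the article sets out a sequence. First, "Before examining the effectiveness of the intervention, the comparability of the two groups will be checked": continuous characteristics by t-test or Mann-Whitney test, dichotomous ones by chi-square test. Then comes the primary analysis at T3, one year after the arrest: "Multiple regression analysis, adjusted for possible differences in baseline characteristics or baseline scores, will be applied". No covariate is named, and no threshold is given for what counts as a difference.

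Under Recruitment and randomisation, allocation takes place after the baseline measurements, in blocks. "The randomisation scheme includes prestratification on two variables, namely hospital site and location of the cardiac arrest", with two envelope series per hospital. Setting names four hospitals, so there are 4 × 2 = 8 strata.

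Table 3 shows which primary instruments have a baseline value. The CIQ has one at T0 (life before the arrest, asked in retrospect at T1), and the SF-36 and EQ-6D have one at T1. The QOLIBRI is measured only at T2 and T3, and the IPA only at T3.

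**The concern.** Patients are randomised after baseline is measured, so a test comparing the groups at baseline asks whether chance produced a difference that is already known to be due to chance. The result says nothing about whether the variable predicts the outcome, and prediction is what makes a covariate useful.

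If adjustment follows observed differences, three things happen. The primary model cannot be written down before the data are seen. A strongly prognostic baseline score is usually left out: if each were tested at the 5% level, a given score would enter in about 5% of trials. Hospital site and arrest location are also usually left out, because stratified blocks make them balance. The analysis then ignores the balance that the design created, and the reported standard error is larger than the true one.

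At stake are the pre-specification of the primary analysis and precision that the collected data could supply.

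**Working it through.** **Inputs from the article** (sample size paragraph in Study population): CIQ mean 16.09, SD 4.20; relevant difference 10%, i.e. 0.10 × 16.09 = 1.609 points (1.609/4.20 = 0.383 SD); one-sided alpha 0.05; power 0.80; 15% loss to follow-up.

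**Inputs assumed, because the article gives none:** the correlation r between baseline and T3 score (0.3, 0.5, 0.7), and the share s of outcome variance explained by the strata (2%, 5%, 10%).

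**1. The plan's own figure.** The article says "an alpha of 0.05 and a power (1-β) of 0.8 would necessitate 84 patients in each group".
- n per group = 2 × (1.645 + 0.842)² × 4.20² / 1.609² = 84.25, which agrees with 84 (85 if rounded up).
- With 84 per group, SE = 4.20 × √(2/84) = 0.648. Then 1.609/0.648 = 2.483, and power = Φ(2.483 − 1.645) = 79.9%.
- Allowing for loss, 170/0.85 = 200.

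This is an unadjusted two-mean formula. It counts on no gain from covariates.

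**2. Always adjusting for the baseline score** multiplies the residual variance by (1 − r²).

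| r | SE | Power at 84 per group | n per group for 80% |
|---|---|---|---|
| 0 | 0.648 | 79.9% | 85 |
| 0.3 | 0.618 | 83.1% | 77 |
| 0.5 | 0.561 | 88.9% | 64 |
| 0.7 | 0.463 | 96.7% | 43 |

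**3. Test-selected against pre-specified adjustment, by simulation.** Settings: 168 analysed, 8 strata, permuted blocks of 4 (block size assumed), 4,000 replicates each. "Test-selected" means that the baseline score enters only if its group difference has p < 0.05, and strata never enter. "Pre-specified" means that the baseline score and strata always enter. With s = 5%:

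| r | Test-selected | Pre-specified |
|---|---|---|
| 0.3 | 80.2% | 84.4% |
| 0.5 | 82.1% | 89.8% |
| 0.7 | 82.1% | 97.9% |

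Monte Carlo error is about 0.6 percentage points. As a cross-check, put residual variance (1 − r² − s) into the formula of step 1. The factors 0.86, 0.70 and 0.46 give 84.9%, 90.7% and 97.8%, close to the last column. Over all settings run, test-selected power was 79% to 83% and pre-specified power 82% to 99%.

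**4. Standard errors and type I error.**
- Test-selected, r = 0.5, s = 5%, no true effect: mean model SE 0.643 against empirical 0.604, and 0.643/0.604 = 1.06, so about 6% too large. One-sided type I error is 4.1%.
- Over all settings, type I error was 2.7% to 4.9% test-selected and 4.5% to 5.4% pre-specified (Monte Carlo error about 0.35 points).
- Omitting only the strata, with the baseline score always in (r = 0.5): 0.562/0.550, 0.562/0.540 and 0.563/0.520, i.e. SE too large by about 2%, 4% and 8% at s = 2%, 5% and 10%.
- Omitting the strata with no baseline score in the model, s = 10%: P(Z > 1.645/√0.90) = P(Z > 1.734) = 4.1%.

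**The case against.** The strongest reply is that the article never says p-values choose the covariates. It gives no threshold, it assigns the tests to baseline characteristics, and it lists baseline scores separately in the regression sentence. That sentence could therefore mean ordinary baseline adjustment, which is the model recommended here. This stands in part: selection by p-value is an inference. But the sentence speaks of adjusting for possible differences, the tests are the only comparability check described, and they come first. The natural reading is that adjustment depends on what is found.

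A second reply is that silence on the strata in a condensed article may be settled in a fuller document. That also stands, and the omission alone is no finding. The point is narrower: the rule that is stated, if applied, would tend to leave out exactly the factors that blocking balances.

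Third, the size rests on assumed values. The CIQ baseline is a retrospective rating of life before the arrest, and its correlation with participation a year later is unknown. At r = 0.3 the gain is about 4 points.

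A reader might also fear that T2 could be taken as the baseline for the QOLIBRI, which has no T1 score. The article does not support this: Data collection defines baseline as T1, and randomisation follows it.

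**Conclusion.** The point holds as one of pre-specification and efficiency. It is worth fixing but is not a defect that invalidates the trial. On the natural reading, the primary model depends on chance imbalance and tends to exclude the variables most worth including.

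With 84 per group, a one-sided 5% test and strata explaining 5% of variance, the power forgone is about 4 points at r = 0.3, 8 at r = 0.5 and 16 at r = 0.7. These figures rest on selection at p < 0.05 and on assumed prognostic strength. If strata explain only about 2% of variance, leaving them out overstates the standard error by only about 2%. The gain from an instrument's own baseline applies to the CIQ, SF-36 and EQ-6D, not to the IPA or QOLIBRI.

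Two stronger conclusions that a reader might draw are not supported. One is that power already budgeted is lost: the sample size never relied on covariates, and the test-selected model keeps about the planned 80%. The other is that the standard errors threaten a false positive: the error is conservative, with type I error at or below nominal.

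**What to change.** Replace the imbalance-based wording with a model that is fixed in advance and used whatever the observed imbalance: T3 outcome on group, hospital site, arrest location and the instrument's own baseline value where one exists (T0 for the CIQ; T1 for the SF-36 and EQ-6D). For the IPA and QOLIBRI, adjust for the two stratification factors; a related baseline score may be added as an optional covariate if it is named in advance. Keep the baseline table, but as description without significance tests. Confine adjustment for observed imbalances to a sensitivity analysis.

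The cost is small, because all these variables are already collected. The one addition needed is a rule for missing T1 scores, since the article foresees missing T1 data and some patients may still be unconscious or incapacitated when consent is sought. Single imputation of the covariate without using the allocation would serve.

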#### Process evaluation

The outcomes of the process evaluation will be reported using descriptive techniques.

#### Economic evaluation

To determine the cost-effectiveness of the intervention a statistical analysis of costs will be performed. The total costs are calculated by adding up direct health care costs, direct non-health care costs and indirect costs. Health care costs are estimated using the Dutch guideline for cost analysis in health care research [50]. The Friction Cost Approach will be used to evaluate production losses, necessary to determine indirect costs [50]. Discounting of costs will take place if significant changes in health care costs take place during the study period. As the distribution of costs might be skewed, differences in costs between the intervention and care-as-usual will be calculated by means of bootstrapping, a method appropriate for any distribution of data.

A multi-way sensitivity analysis will be performed to gain insight into the generalisability of the economic evaluation.

A cost-utility analysis will relate the difference in between the intervention and care-as-usual to changes in utility. This will result in costs per quality-adjusted-life-years (QALY's).

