## Methods/Design

### Study design

The study presented in this paper is a randomised, controlled clinical trial in which the effect of an early intervention service will be investigated. Participants will be followed over one year. During this year, three measurements will take place, namely two weeks, three months and twelve months after the cardiac arrest (see flow diagram, Figure 1). The Medical Ethics Committee of University Hospital Maastricht/Maastricht University approved the study protocol. The study is registered in a public trial registry [ISRCTN74835019]. This study is part of a larger research project, which also comprises a prospective and prognostic cohort study.

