### Determination of costs

Data concerning costs will be gathered prospectively using monthly cost-diaries [49]. All the participants receive cost-diaries in which they are asked to note all their health care utilisation during that month. To prevent non-compliance, the research assistant will give a phone call at the end of each month and will record the health care utilisation of that month. For the calculation of the total costs, three categories can be distinguished, namely direct health care costs, direct non-health care costs and indirect costs. For the determination of the direct health care costs the following variables will be recorded: duration admission in health care facility, visits physicians and other health care providers and amount of prescribed medication. Direct non-health care costs that will be measured, are the costs of informal health care, over-the-counter medication, costs of health activities, hours of paid or unpaid household help and special aids. The indirect costs comprise loss of paid and unpaid work productivity of the patient.

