Fourth, we explicitly chose to include the strain for and quality of life of the caregiver in the secondary outcome measures. Our impression is that being the partner of a cardiac arrest survivor can imply a heavy burden. These caregivers are at risk for developing stress and emotional problems and this definitely needs more attention. Therefore, the intervention is directed at both the patient and their caregiver, who is expected to benefit from the early intervention service as well.

To conclude, this paper describes the design of a randomised, controlled clinical trial that will investigate the effectiveness of a new early intervention service for cardiac arrest survivors and their caregivers. The inclusion of the participants started in April 2007 and will continue until April 2010. The results of this study will provide evidence on the effectiveness of this early intervention service, as well as the cost-effectiveness and its feasibility. This will give insight into the question whether it would be useful to implement this early intervention service in the Dutch health care system.

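### Discounting of costs is made to depend on changes in health care costs, which is not what discounting corrects for, and each participant's horizon is only 12 months

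*Protocol article*

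**What the plan says.** The rule stands in the protocol article under Statistical analysis, Economic evaluation: "Discounting of costs will take place if significant changes in health care costs take place during the study period". The same section says of valuation: "Health care costs are estimated using the Dutch guideline for cost analysis in health care research". It then plans a bootstrapped comparison of costs between the arms and a cost-utility analysis giving a cost per QALY.

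Three other places bear on the rule:

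- Study design: "Participants will be followed over one year".
- Discussion: "The inclusion of the participants started in April 2007 and will continue until April 2010".
- Determination of costs: "Data concerning costs will be gathered prospectively using monthly cost-diaries". What is recorded there is mainly volume, such as length of admission, visits, amount of medication, hours of help and lost work.

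**The concern.** Two different corrections seem to have been merged. Discounting expresses time preference, and it matters when costs or effects fall in later years of the horizon. Changes in price level call for conversion to a common price year. The rule uses a trigger that could suggest the second correction and then applies the first.

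No reading of the trigger makes discounting the right response:

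- If it means prices, the remedy is a common price year.
- If it means volume of care, no correction is due, because a change in volume is part of what the trial measures.
- If all care is valued at one set of unit prices, price changes during the study do not enter the data at all.

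At stake are total costs and the cost per QALY in an economic evaluation that is one of the stated aims and is meant to inform implementation in Dutch health care.

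**Working it through.** **Inputs.** The horizon is 12 months per participant (Study design). Recruitment runs from April 2007 to April 2010 (Discussion). With 12 months of follow-up, costs arise until about April 2011, a span of 4 years. The article gives no discount rate, base date, price year or inflation rate, so there is no figure of the plan's own to reproduce. All rates below are assumptions.

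**Step 1: what discounting depends on.** The factor is 1/(1+r)^t, with r the annual rate and t the time in years from the base date. No price term enters it, and for positive r it never exceeds 1. It can only lower a cost or leave it unchanged.

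**Step 2: discounting within each participant's 12 months.** For costs spread evenly over the year, the mean factor is (1 − 1/(1+r)) / ln(1+r).

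| Assumed r | Mean factor | Total cost lowered by |
|---|---|---|
| 1.5% | 0.01478/0.01489 = 0.9926 | 0.7% |
| 3% | 0.9854 | 1.5% |
| 4% | 0.9806 | 1.9% |
| 5% | 0.04762/0.04879 = 0.9760 | 2.4% |

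A single cost at month 12 would be lowered by 1 − 1/1.015 = 1.5% to 1 − 1/1.05 = 4.8%. Costs early in the year would be lowered less.

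**Step 3: discounting by calendar date.** If costs were instead discounted at 4% to April 2007, the latest ones (t = 4) would be lowered by 1 − 1/1.04^4 = 14.5%, and those of April 2007 (t = 0) not at all. The 14.5% is therefore a maximum and not an average.

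**Step 4: direction.** Take a cost of 100 at April 2007 prices, incurred at year 2 and valued at the prices of that time. Let prices change by g a year and discount at 4% to 2007.

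| g | Cost at year 2 | Discounted | At 2007 prices | At 2011 prices |
|---|---|---|---|---|
| +3% | 100 × 1.03² = 106.1 | 106.1/1.04² = 98.1 | 100.0 | 106.1 × 1.03² = 112.6 |
| −3% | 100 × 0.97² = 94.1 | 94.1/1.04² = 87.0 | 100.0 | 94.1 × 0.97² = 88.5 |

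Discounting moves the cost the wrong way when prices rise and the price year is 2011, and when prices fall and the price year is 2007. In the other two cases the direction agrees and only the size is wrong. Discounting matches indexing only by coincidence, for example when r equals g and the base is 2007.

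If one fixed set of unit prices is applied to the recorded volumes, the cost is the same at every date. No price correction is then needed.

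**Step 5: effect on the comparison.** Allocation "will be performed centrally by the project leader using a computerised block randomisation", stratified by hospital and location of arrest, so both arms are spread over the same calendar period. If the same mean factor k applies in each arm, the cost difference becomes k × (intervention − control) and keeps its sign. The factor could differ slightly if one arm's costs fall earlier in the year. Within 12 months, however, every individual factor lies between 0.952 and 1 at 5%, so the sign is at risk only if the difference is already close to zero.

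**The case against.** The case on the other side has real force. This is a condensed article. Price year, index and rate are commonly left to the full protocol or an economic analysis plan, so their absence is no finding. The cited costing guideline may deal with indexing. The rule is conditional and may never be triggered, and it may be a slip of terminology for price adjustment. The diaries record mainly volumes, so a single set of unit prices would remove most calendar drift. The effect is small, falls on both arms and does not touch the clinical outcomes.

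All of this limits the size of the problem, and I accept it. It does not rescue the sentence, which is a positive rule: it names a correction and a trigger, and the two do not belong together. The reference to the guideline comes earlier in the same section and does not alter the rule.

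A reader might infer more than the article supports:

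- *That costs would be moved in the wrong direction.* Step 4 shows that this holds for some choices of price year and not for others, and the article does not say that contemporaneous prices will be used.
- *That the result would depend on date of enrolment.* As an effect of discounting, this needs a calendar base, which the article does not state. Discounting from each participant's own start date has no such effect.
- *That a cut of up to 14.5% replaces an increase that inflation would require.* The largest cut falls on the last costs. Under a last-year price base it is the first-year costs that need raising, and calendar discounting leaves those unchanged. The two cannot be set against each other.
- *That discounting costs but not QALYs is a separate flaw.* Over 12 months neither needs discounting, so this adds nothing.

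**Conclusion.** The rule is wrong as written, and its likely effect is modest. If triggered, it would lower total costs by about 0.7% to 2.4%, given discounting within each participant's 12 months, costs spread evenly over the year and rates of 1.5% to 5%. A larger effect, up to 14.5% for the latest costs, requires an assumed 4% rate and a base date of April 2007 that the article does not give. On either base, any real price change over the roughly four calendar years would remain uncorrected if contemporaneous prices are used. The error would mainly rescale the cost difference and the cost per QALY, and a reversal is not to be expected. The primary and secondary clinical analyses are unaffected.

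**What to change.** Replace the discounting sentence in Economic evaluation with:

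> Costs and QALYs are not discounted because follow-up is 12 months. All costs are expressed in one stated price year, using a price index where the source year differs.

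The price year and index can be named in the analysis plan. If one set of unit prices is applied to the recorded volumes, only items taken from another source year or recorded directly in money would need conversion. The change is one sentence with trivial analysis work. It needs no new data and does not affect the sample size or the clinical analysis.
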